## Abstract

**Introduction:**

Type 2 diabetes patients have abdominal obesity and low thigh circumference. Previous studies have mainly focused on the role of exercise in reducing body weight and fat mass, improving glucose and lipid metabolism, with a lack of evaluation on the loss of muscle mass, diabetes complications, energy metabolism, and brain health. Moreover, whether the potential physiological benefit of exercise for diabetes mellitus is related to the modulation of the microbiota-gut-brain axis remains unclear. Multi-omics approaches and multidimensional evaluations may help systematically and comprehensively correlate physical exercise and the metabolic benefits.

**Methods and Analysis:**

This study is a randomized controlled clinical trial. A total of 100 sedentary patients with type 2 diabetes will be allocated to either an exercise or a control group in a 1:1 ratio. Participants in the exercise group will receive a 16-week combined aerobic and resistance exercise training, while those in the control group will maintain their sedentary lifestyle unchanged. Additionally, all participants will receive a diet administration to control the confounding effects of diet. The primary outcome will be the change in body fat mass measured using bioelectrical impedance analysis. The secondary outcomes will include body fat mass change rate (%), and changes in anthropometric indicators (body weight, waist, hip, and thigh circumference), clinical biochemical indicators (glycated hemoglobin, blood glucose, insulin sensitivity, blood lipid, liver enzyme, and renal function), brain health (appetite, mood, and cognitive function), immunologic function, metagenomics, metabolomics, energy expenditure, cardiopulmonary fitness, exercise-related indicators, fatty liver, cytokines (fibroblast growth factor 21, fibroblast growth factor 19, adiponectin, fatty acid-binding protein 4, and lipocalin 2), vascular endothelial function, autonomic nervous function, and glucose fluctuation.

**Discussion:**

This study will evaluate the effect of a 16-week combined aerobic and resistance exercise regimen on patients with diabetes. The results will provide a comprehensive evaluation of the physiological effects of exercise, and reveal the role of the microbiota-gut-brain axis in exercise-induced metabolic benefits to diabetes.

**Clinical Trial Registration:**

http://www.chictr.org.cn/searchproj.aspx, identifier ChiCTR2100046148.

## Introduction

Diabetes mellitus is a global health challenge, which is estimated to affect 783.2 million people by 2045 (1). Abdominal obesity is a common somatotype in patients with type 2 diabetes, while some studies have reported that type 2 diabetes patients also have a low thigh circumference (2, 3), which becomes more obvious with age (4). Low femoral subcutaneous fat is associated with unfavorable glucose and lipid levels (5), and thigh muscle mass area is inversely associated with future insulin resistance (6). Sarcopenia is an age-related process that occurs commonly in the elderly population, with a progressive skeletal muscle disorder involving the accelerated loss of muscle mass and function (7). Currently, sarcopenia in type 2 diabetes, a condition known as secondary sarcopenia, has gained increased attention (8). Exercise is considered as one of the effective therapeutic methods for type 2 diabetes and sarcopenia. Previous studies have mostly focused on the effect of exercise on obesity and visceral fat accumulation in type 2 diabetes, while its action on low thigh circumference has rarely been explored.

In the recent decades, the relationship between diabetes and brain health has gradually attracted attention (9–11). Diabetes has been identified as a key risk factor for mild cognitive impairment and dementia (12). Appetite is also altered in patients with obesity and type 2 diabetes. The brain domains of obese people are more sensitive to hunger and have increased activation of reward regions for visual food cues (13). In addition, diabetes is often accompanied by changes in subjective mood states and emotional behavior, such as depression (14, 15). Previous studies have shown that exercise can improve cognitive impairment (16), appetite (17), and depression (18), while most of them have evaluated the brain function using questionnaires and scales. At present, functional magnetic resonance imaging (fMRI) is the mainstay of neuroimaging in cognitive neuroscience, providing a method to investigate the possible causal relationship between brain activity and behavior (19, 20). A recent clinical trial performed in Hong Kong reported that gut microbiota and metabolites mediated exercise-induced metabolic benefits to prediabetic men (21). Exercise affects the gut microbiota composition and microbial metabolites (22), while gut microbiota and their metabolites are involved in regulating behavior and brain activity, including stress response, emotion, pain, feeding behavior, and cognition (23, 24). However, there is a paucity of research elucidating whether the potential physiological benefits of exercise for diabetes mellitus are related to the modulation of the microbiota-gut-brain axis.

Herein, we introduce a detailed design of effects of exercise intervention on type 2 diabetes patients with abdominal obesity and low thigh circumference (EXTEND) study. We will enroll sedentary diabetes patients with abdominal obesity and low thigh circumference and explore the effect of combined aerobic and resistance exercise. The primary purpose of this trial is to clarify the role of exercise on abdominal obesity and loss of muscle mass, which will be accurately quantified using magnetic resonance imaging (MRI). Furthermore, many studies conducted on type 2 diabetes demonstrate that exercise intervention improves anthropometric, metabolic, and clinical indicators, with a lack of assessment of energy metabolism, diabetes complications, and brain health. There is an urgent need for more clinical researches with comprehensive evaluation and accurate measurement to investigate the role of exercise in type 2 diabetes. Thus, we aim to provide a multidimensional evaluation of the role of exercise through a broad assessment of clinical parameters, including anthropometric measurements, information of clinical status and lifestyle, biochemical indicators, psychosocial characteristics, accurate imaging examination, exercise-related indicators, and so on. Moreover, multi-omics analysis, such as metagenomics, metabolomics, proteomics, and single-cell sequencing, will be conducted. We believe that a comprehensive collection of clinical indicators and multi-omics data will provide a foundation for clinical research on diabetes, and the role of the microbiota-gut-brain axis in the benefits of exercise for diabetes will be elucidated.

## Methods and Analysis

### Study Design

This study is a randomized controlled clinical trial. The participants will be randomized into two groups in a 1:1 ratio: exercise intervention and sedentary control group. The participants (50 participants per group) will undergo a 16-week intervention. Participants in the control group will maintain their sedentary lifestyle unchanged, and the exercise intervention group will receive combined aerobic and resistance exercise training. Moreover, all participants will be required to undertake a balanced diet to reduce the confounding effects of different dietary habits. The study design is outlined in **Figure 1**.

**Figure 1 f1:**
[figure not shown]
Overview of the study design. After screening and a 1-week run-in period, eligible participants are randomly assigned to either exercise group or control group (n = 50 per group) for 16-week intervention. During the whole trial, participants in exercise group receive combined aerobic and resistance exercise training three times a week, and control group maintain their sedentary lifestyle unchanged. All participants receive a diet administration during the intervention. In addition, participants take part in a follow-up visit every four weeks.

### Participants and Recruitment

The study will include adults aged 35-65 years of any sex, who have been diagnosed with type 2 diabetes mellitus and are not insulin-dependent. Potential participants will be recruited at the Shanghai Jiao Tong University Affiliated Sixth People’s Hospital. The inclusion and exclusion criteria are presented in **Table 1**. The potential benefits and risks of the study will be informed to the participants before screening. Written informed consent will be obtained from all participants. Physicians will conduct a preliminary clinical evaluation to screen eligible participants, including anthropometric measurement (e.g., height, weight, body mass index, and waist, hip, and thigh circumference), blood pressure, glycated hemoglobin (HbA1c), kidney function assessment, basic information (e.g., age, sex, menopause, education, and occupation), and the questionnaire information collection (lifestyle habits, family history, and disease and medication records). If participants meet all the criteria, they will be invited to enter a run-in period, which will be followed by randomization of participants who complete the run-in period.

**Table 1 T1:** Inclusion and exclusion criteria.

Inclusion Criteria
Diagnosed with type 2 diabetes mellitus; Not more than three antidiabetic agents; The use of antidiabetic agents is stable for at least 6 weeks, and remains unchanged during the study intervention; Aged 35 to 65 years old; Abdominal obesity: waist circumference ≥ 90 cm for males and ≥ 80 cm for females; Body mass index ≤ 35 kg/m^2^; Waist to thigh ratio (WTR): male ≥ 1.7, female ≥ 1.6; Sedentary lifestyle (≤ 60 minutes of moderate-intensity activities per week).
**Exclusion Criteria**
Glycated hemoglobin < 6.5% or ≥ 9%; Insulin usage; Presence of one or more of the following complications: severe proliferative diabetic retinopathy or worse, macroalbuminuria (urine albumin-creatinine ratio ≥ 300 mg/g), or renal dysfunction (eGFR ≤ 60 ml/min/1.73m^2^); History of cardiovascular events, including myocardial infarction, percutaneous coronary intervention, unstable angina, heart failure, and cardiac insufficiency; History of cerebrovascular diseases, including hemorrhagic and ischemic stroke; Muscle, bone, or neuromuscular injuries, and so on that will prevent exercise training; Severe osteoporosis, or suboptimal bone density test results even after treatment; Pregnancy; Not able or unwilling to undergo magnetic resonance imaging, including claustrophobia, implantable cardioverter defibrillator and pacemaker;

10. Diagnosed depression or any mental illness rendering the patients unable to understand the nature, scope and schedule of the study; 11. atients who take drugs that are unstable or affect glucose metabolism.

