### Intervention

#### Exercise Intervention

Based on cardiopulmonary fitness and one repetition maximum, an individualized exercise training (combined aerobic and resistance exercises, three sessions per week) regimen will be developed. Each practice session will take 80 minutes, including 10 minutes of warm-up, 15 minutes of aerobic exercise, 10 minutes of resistance training, 10 minutes of rest, 15 minutes of aerobic exercise, 10 minutes of resistance training, and 10 minutes of relaxation. Aerobic and resistance exercises will include training with magnetic exercise bikes (HG-HRUB150T) and chest press/rowing (KY-701), abdominal and back muscle training (KY-705), and leg kick and hook (KY-703) machines (Nanjing Kuanyue Health Technology Co., Ltd, Nanjing, China). All aerobic and resistance training data will be recorded by an intelligent detection software system (Nanjing Kuanyue Health Technology Co., Ltd, Nanjing, China). The exercise training will be progressive and variable. Aerobic exercise programs will be divided into four training cycles (four weeks per cycle) and resistance exercise programs will be divided into three cycles. The differences in the training cycles will primarily be reflected in terms of the intensity and load. Details of exercise intervention are shown in **Table 3**.

**Table 3 T3:** Protocol of exercise intervention.

Phase	Week	Intensity	Load
Aerobic Exercise			
I	1 – 4 weeks	40% VO_2max_	Males: 35 W; Females: 25 W
II	5 – 8 weeks	50% VO_2max_	Males: 40 W; Females: 30 W
III	9 – 12 weeks	60% VO_2max_	Males: 45 W; Females: 35 W
IV	13 – 16 weeks	70% VO_2max_	Males: 50 W; Females: 40 W

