**Resistance Exercise**			
I	1 – 6 weeks	50% 1RM	1-2 weeks: 8 times/muscle group * 2 group
			3-4 weeks: 10 times/muscle group * 2 group
			5-6 weeks: 12 times/muscle group * 2 group
II	7 – 12 weeks	60% 1RM	7-8 weeks: 8 times/muscle group * 2 group
			9-10 weeks: 10 times/muscle group * 2 group
			11-12 weeks: 12 times/muscle group * 2 group
III	13 – 16 weeks	65% 1RM	13-14 weeks: 8 times/muscle group * 2 group
			15-16 weeks: 10 times/muscle group * 2 group

Exercise intensity will be monitored and instructed using Rating of Perceived Exertion, with scope definition of 12 - 16. The intensity of exercise can be adjusted according to the weight and actual condition of participants. 1RM, 1 repetition maximum; VO_2max_, maximum oxygen uptake.

Participants in the exercise group will take part in exercise training at the Shanghai Jiao Tong University Affiliated Sixth People’s Hospital under the guidance of professional coaches. The duration and intensity of each exercise session will be recorded, and the coach will make personalized adjustments to the exercise intensity of each participant. The blood pressure, heart rate, and finger-stick blood glucose of participants will be recorded before and after the exercise session.

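### Read literally, the retinopathy exclusion in Table 1 leaves proliferative disease below the severe grade eligible for progressive exercise training

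*Protocol article*

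**What the plan says.** The exclusion list in Table 1 has one item on diabetic complications. It opens with "Presence of one or more of the following complications", so any single listed complication is enough to exclude. The eye limit is "severe proliferative diabetic retinopathy or worse". The other limits in the item are renal: "macroalbuminuria (urine albumin-creatinine ratio ≥ 300 mg/g), or renal dysfunction (eGFR ≤ 60 ml/min/1.73m^2" (units as printed).

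The only criterion framed around fitness to exercise is "Muscle, bone, or neuromuscular injuries, and so on that will prevent exercise training", which is built on musculoskeletal and neuromuscular problems.

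Under Participants and Recruitment, physicians carry out the preliminary evaluation, and the information collected includes "lifestyle habits, family history, and disease and medication records".

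Under Exercise Intervention, the exercise group trains on "combined aerobic and resistance exercises, three sessions per week", for 16 weeks, with intensity rising by phase (Table 3). The note to Table 3 holds perceived exertion at 12 to 16 and adds: "The intensity of exercise can be adjusted according to the weight and actual condition of participants". Coaches supervise, and blood pressure, heart rate and finger-stick glucose are recorded before and after each session. Under Data Management and Monitoring, serious adverse events go at once to an independent Data Monitoring Committee, the principal investigator and the Ethics Committee.

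**The concern.** An eligibility threshold is applied as written. This one sets a grade within proliferative retinopathy rather than at its onset, so its plain meaning admits proliferative disease that a screener would not call severe.

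The plan itself lists retinopathy among the complications that bar entry, so the line has a protective purpose. At stake is whether it serves that purpose for patients who may be assigned to training of rising intensity.

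The phrase also reads oddly. A threshold that ends with *or worse* normally leaves room above it, and above the severe end of proliferative disease there is little. Either the threshold is meant literally, or the words do not say what was intended. In both cases the line needs attention, because two screeners could decide differently about the same patient.

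**Working it through.** The plan gives no figure on this point, so the check is mainly a reading of the text.

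1. **Does the criterion exclude all proliferative retinopathy?** As printed, no. The adjective restricts the exclusion to the severe grade and anything beyond it.

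2. **Does another criterion close the gap?** No other item in Table 1 mentions retinopathy or the eye.
   - The item on injuries that prevent exercise is open-ended in its wording, but its subject is muscle, bone and nerve, and it gives no retinopathy grade.
   - The limits on HbA1c, insulin use, kidney disease and vascular history may remove some patients with advanced microvascular disease. That is inference, and none of them is an eye criterion.

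3. **Does any later step act as an eligibility rule?** Each safeguard in turn:
   - Physician review of disease records can reveal retinopathy, but the physician then applies the printed threshold.
   - The exertion range, coach adjustment and session measurements govern how a participant trains after entry.
   - Serious adverse event reporting and the Data Monitoring Committee act after an event.
   - None of these is linked to retinopathy.

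4. **Whom does the rule reach?** It applies before randomization, so it governs entry for all 100 planned patients. The training programme applies only to the 50 assigned to exercise.

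5. **How many would be affected?** The article does not say how common proliferative retinopathy below the severe grade is among candidates. No count and no risk estimate can be derived.

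6. **Is the sample size touched?** The inputs under Sample Size Estimation are a 1.2 kg difference, a standard deviation of 1.9 kg, two-sided α of 0.05, 80% power and 20% loss.
   - n per group = 2 × (1.960 + 0.842)² × 1.9² / 1.2² = 2 × 7.85 × 3.61 / 1.44 = 39.4, rounded up to 40.
   - Allowing for loss: 40 / (1 − 0.20) = 50 per group, or 100 in total.
   - This reproduces the plan. No input depends on retinopathy, and the target counts enrolled patients, so excluding a few more candidates at screening leaves power and type I error as they are.

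**The case against.** The strongest reply is that nothing in the document shows the printed grade to be wrong. The article never says that proliferative disease below the severe grade is unsafe for this programme. The view that *or worse* has little to refer to leans on a grading scale that the article does not reproduce. The threshold could be a deliberate clinical choice or a slip in a condensed article whose full protocol reads correctly. Supervision, the exertion range, physician screening and independent safety monitoring all reduce the risk.

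Much of this stands. It rules out any claim of demonstrated harm and limits the number of patients in question. It does not remove the point: the article states a threshold rather than leaving it to another document, and the safeguards do not alter who may enter.

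A reader might also infer more than the documents support:

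- **That the line is a misprint for severe non-proliferative disease.** This is plausible, but nothing in the article confirms it. Adopting that grade unchecked would add an exclusion on a guess.
- **That the renal limits in the same item prove the eye limit wrong.** The plan does not say that cut-offs for different organs must match in stage, so the comparison carries little weight.
- **That the peak training intensities measure the hazard.** They describe the programme for every exercise participant, and the article does not link them to retinal risk.
- **That no eye assessment takes place.** An article may leave screening procedures to the full protocol, so its silence shows nothing.

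**Conclusion.** The point holds as a defect in a stated safety criterion: read literally, proliferative retinopathy below the severe grade remains eligible, and the phrase is doubtful on its own terms. It should be corrected.

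Its practical size is probably small. Few patients are likely to be affected, no harm estimate can be given, and the statistical properties of the trial are unchanged.

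The conclusion rests on two assumptions: that screeners apply the wording as printed, and that the criterion is meant to keep proliferative disease as such out of the programme. The second is a clinical judgement that the document does not spell out. If the full protocol carries different wording and screening followed that, only the article needs correcting.

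**What to change.** Change the retinopathy wording in Table 1 to exclude any proliferative diabetic retinopathy. This closes the gap without adding a non-proliferative exclusion.

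Compare the line with the full protocol. Set the threshold at severe non-proliferative diabetic retinopathy or worse only if the full protocol confirms that this grade was intended.

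If the printed wording was used at screening, check the recorded retinopathy status of patients already enrolled, at most 100.

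The cost is one corrected line, a few more excluded candidates and, where needed, one review of existing records. The sample size and the analysis stay as they are.

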### Randomization and Blinding

The randomization digital table is generated using a computer. Participants will be randomly assigned to the exercise or control group in a 1:1 ratio stratified by age and sex. The group assignment will be performed by an independent statistician who would be blinded to the recruitment, intervention, and evaluation of participants. Blinding of participants and researchers (who provide exercise instructions) to group assignment would not be possible due to the specific nature of the study. However, the researchers and statisticians who perform the follow-up assessments and statistical analyses will be blinded to group assignment.

### Data Collection and Follow-Up

Participants will participate in baseline, 4, 8, 12, and 16-week follow-up visits at the Department of Endocrinology and Metabolism, Shanghai Jiao Tong University Affiliated Sixth People’s Hospital. **Table 2** shows the schedule of the study process. The clinical assessments, measurements, and data collection will be conducted by independent researchers who have been trained before the study. Apart from the anthropometry and hematology examination, physicians will also perform a series of clinical assessments, including bioelectrical impedance analysis, MRI of abdomen and lower limbs, magnetic resonance spectroscopy, liver transient elastography, endothelial function ultrasound, flash glucose monitoring, heart rate variability analysis, and exercise-related tests (**Table 2**). The international physical activity questionnaire will be completed to evaluate habitual physical activity over the previous seven days, and a three-dimensional accelerometer tester (wGT3x-BT, Manufacturing Technology Inc, MTI, Florida, America) will be used to continuously monitor the basal physical activity over the following seven days on visit 1, 3, and 5. The dietary habits will be assessed through the three-day food record and food frequency questionnaire. In addition to assessment through conventional questionnaires (e.g., 100-mm visual analog scale, Patient Health Questionnaire-9, Generalized anxiety Disorder scale-7, Problem Areas in Diabetes scale, and Montreal Cognitive Assessment Scale), the brain health of the participants will be accurately evaluated by fMRI. All questionnaires will be filled by participants with the help of trained researchers during a face-to-face interview. Furthermore, blood, urine, stool, and saliva samples will be collected before and after intervention for further multi-omics analysis. Detailed methods of measurements and evaluations are described in the **Supplementary Material**.

**Table 2 T2:** Schedule of the study process.

Time point	Screening	Visit 1	Visit 2	Visit 3	Visit 4	Visit 5
	-2 weeks ~ 0 week	0week	4 weeks	8 weeks	12 weeks	16 weeks
**Eligibility screening**	✓					
**Informed consent**	✓					
**Anthropometrics** (height, weight, body mass index, and waist, hip, and thigh circumference)	✓	✓	✓	✓	✓	✓
**Bioelectrical impedance analysis** (fat mass and percentage, lean mass and percentage)		✓	✓	✓	✓	✓
**Biochemical indicators** (liver enzyme, renal function, blood glucose, insulin, C peptide, and blood lipid)		✓		✓		✓
**HbA1c**	✓			✓		✓
**Cytokines** (FGF21, FGF19, FABP4, LCN2, adiponectin, etc.)		✓		✓		✓
**Appetite related hormones** (GLP-1, ghrelin, PYY, etc.)		✓		✓		✓
**Magnetic resonance imaging**		✓		✓		✓
**Functional magnetic resonance imaging**		✓				✓
**Magnetic resonance spectroscopy**		✓		✓		✓
**Liver transient elastography**		✓		✓		✓
**Endothelial function ultrasound**		✓		✓		✓
**Exercise-related tests** (cardiopulmonary fitness test, three-dimensional accelerometer test, muscle oxygen monitoring, physical fitness test)		✓		✓		✓
**Isolation of peripheral blood monocytes**		✓		✓		✓
**Heart rate variability analysis**		✓		✓		✓
**Flash glucose monitoring**		✓				✓
**Metagenomic analysis**		✓				✓
**Metabolomic analysis**		✓				✓
**Questionnaires** (International physical activity questionnaire, three-day food record, food frequency questionnaire, 100-mm VAS, PHQ-9, GAD-7, PAID, MoCA)		✓		✓		✓

FABP4, fatty acid-binding protein 4; FGF, fibroblast growth factor; GAD-7, Generalized anxiety Disorder scale-7; GLP-1, glucagon-like peptide-1; HbA1c, glycated hemoglobin; LCN2, lipocalin 2; MoCA, Montreal Cognitive Assessment scale; PAID, Problem Areas in Diabetes Scale; PHO-9, Patient Health Questionnaire-9; PYY, peptide YY; VAS, visual analog scale.

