#### Secondary Outcomes

Secondary outcomes include change rate of body fat mass, and changes in lean mass and percentage, anthropometric indicators (body weight, body mass index, and waist, hip, and thigh circumference), clinical biochemical indicators (HbA1c, insulin sensitivity, liver enzyme, renal function, blood lipid, blood glucose, serum insulin and C peptide), brain health (appetite, mood, and cognitive function), immunologic function, metagenomics, metabolomics, energy expenditure, cardiopulmonary fitness (maximum oxygen uptake, maximum oxygen uptake/predicted oxygen uptake), exercise-related indicators (physical activity, grip, flexibility, lower limb muscle endurance and strength, static and dynamic balance function, and muscle oxygen), fatty liver, cytokines (fibroblast growth factor [FGF] 21, FGF19, adiponectin, fatty acid-binding protein 4, and lipocalin 2), vascular endothelial function, autonomic nervous function, and glucose fluctuation.

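### The accelerometer looks forward from each visit, so as written its visit-5 week falls after training has ended and, unless an unstated gap exists, its baseline week falls in training week 1

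*Protocol article*

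**What the plan says.** All references are to the protocol article.

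- **Wear window.** Under Data Collection and Follow-Up, the accelerometer "will be used to continuously monitor the basal physical activity over the following seven days on visit 1, 3, and 5".
- **Questionnaire window.** The same sentence gives the self-report instrument the opposite direction: "The international physical activity questionnaire will be completed to evaluate habitual physical activity over the previous seven days".
- **Visits.** "Participants will participate in baseline, 4, 8, 12, and 16-week follow-up visits". Table 2 puts visit 1 at week 0, visit 3 at week 8 and visit 5 at week 16, and ticks both instruments at these three visits.
- **Order of events.** The Figure 1 legend: "After screening and a 1-week run-in period, eligible participants are randomly assigned to either exercise group or control group". The screening column of Table 2 ends at week 0, so the run-in appears to be over by visit 1.
- **Training.** The same legend: "During the whole trial, participants in exercise group receive combined aerobic and resistance exercise training three times a week". Table 3 runs both components from week 1 to week 16.
- **Outcome.** The Secondary Outcomes list includes "exercise-related indicators (physical activity, grip, flexibility" and further items. Table 2 files the accelerometer under the matching heading of exercise-related tests.
- **Analysis.** Statistical Analysis compares changes between arms by analysis of covariance with the baseline level as covariate, and also plans mixed-effect models.
- **Blinding.** Randomization and Blinding states that participants cannot be blinded.

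**The concern.** A baseline should be recorded before allocation can influence it, and an end-of-intervention value while the intervention is still running. A window that opens at week 0 and another that opens at week 16 appear to miss on both counts. In the exercise arm, the first would contain supervised training and the last would not.

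Two things are at stake. First, the accelerometer-based change would understate what exercise adds, and adjusting for a baseline that treatment has already altered does not repair this. Second, the accelerometer is the only objective measure of free-living activity that the article names for both arms. Its final reading would not show whether controls were still sedentary at the end of the intervention.

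**Working it through.** **1. Training volume (Exercise Intervention section).** The session parts sum to the stated length: 10 + 15 + 10 + 10 + 15 + 10 + 10 = 80 min. Active work is (15 + 15) aerobic + (10 + 10) resistance = 50 min. At three sessions a week, T = 3 × 50 = 150 min/week.

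**2. Overlap of each window with training.** Let visit 1 be day 0 and let g be the gap in days before the training period starts. Training covers days g + 1 to g + 112 (16 × 7 = 112). Each window is the seven days after its visit. The article does not give g, so a range is shown. Entries are training-period days inside the window.

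| Assumed gap g | Weeks counted from | Visit 1 | Visit 3 | Visit 5 |
|---|---|---|---|---|
| 0 | either | 7 of 7 | 7 of 7 | 0 of 7 |
| 3 | first session | 4 | 7 | 0 |
| 3 | visit 1 | 4 | 7 | 3 |
| 7 | first session | 0 | 7 | 0 |
| 7 | visit 1 | 0 | 7 | 7 |

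Only the last row clears both ends. It puts visit 5 a week before training finishes, which fits poorly with the article's plan to collect samples before and after the intervention. On any reading that keeps visit 5 post-intervention, its window contains no training. The visit-1 result depends on g.

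**3. Direction of the bias when g = 0.** Let c be the share of T that the device captures, and s the lasting rise in non-training activity. Assume that s is zero in week 1 and equal in weeks 16 and 17, and that controls do not change. Neither c nor s is in the article.

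- Aligned windows (before training, and training week 16): change = s + cT.
- Windows as written (training week 1, and the week after training): change = s − cT.

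With T = 150 and s = 60 (assumed):

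| c (assumed) | Aligned | As written |
|---|---|---|
| 0 | +60 | +60 |
| 0.25 | +97.5 | +22.5 |
| 0.5 | +135 | −15 |
| 1 | +210 | −90 |

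The sign changes only if s < cT. With s = 120 and c = 0.5, the as-written change is 120 − 75 = +45, with no reversal.

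**4. Effect of baseline adjustment.** The adjusted arm difference is the follow-up difference minus b times the baseline difference, where b is the within-arm slope on baseline (not given; assumed between 0 and 1). With g = 0 this is s − b·cT, against s + cT for aligned windows. The shortfall is (1 + b)cT, so adjustment reduces the bias at best and does not remove it. At c = 0.5 and s = 60, the adjusted estimate is 60 − 75b, which is negative only if b > 60/75 = 0.8.

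**5. Visit 3.** Here the follow-up window lies inside training. With g = 0, the unadjusted change from visit 1 is (s + cT) − cT = s. It loses the training component but does not reverse.

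**6. The two instruments side by side.** At visit 1 the questionnaire covers the week before, and at visit 5 it covers training week 16. With g = 0 the accelerometer covers training week 1 and the week after training. They describe different weeks at every visit and cannot corroborate each other.

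**The case against.** The strongest reply is that the article never dates the first session or randomisation relative to visit 1. Training is individualised from fitness tests, and Table 2 schedules the cardiopulmonary test at visit 1, so some gap is plausible; a gap of seven days would clear the baseline window. This stands, and the baseline half of the point is therefore conditional. It does not rescue the visit-5 half.

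Second, the stated target is basal activity, and supervised work is logged separately by the training software. If sessions are excluded, c = 0 and session minutes cause no bias. This also stands as a possible reading. However, the text calls for continuous monitoring and gives no rule for removing sessions. Even on that reading, without a gap the first window follows an unblinded allocation, and the last still falls outside the intervention.

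Third, the questionnaire measures the same secondary outcome over well-placed weeks. That is correct and limits the damage, although it is self-report in an unblinded trial. In addition, the forward windows at visits 1 and 3 do no harm to the check on controls, who do not train; for them only the visit-5 window is misplaced.

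Fourth, detailed methods are in a supplement that is not shown. The article nevertheless states the window itself, so the point concerns a stated rule and not a missing detail.

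**Conclusion.** The concern holds in limited form, with minor to moderate severity. The firm part is that the visit-5 accelerometer week, as written, follows the end of training and so does not measure activity during the intervention in either arm. This assumes only that visit 5 is the post-intervention visit. The conditional part is that, with no gap after visit 1, the baseline is a post-allocation, arm-affected covariate. The accelerometer-based change is then biased against exercise by up to (1 + b)cT in the adjusted analysis. Because b and c are not in the document, the size cannot be derived from it.

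A reader might infer more than this:

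- **That the sign of the physical-activity outcome will be reversed.** The documents do not support this. Reversal needs captured training to exceed any lasting rise in other activity, and the questionnaire version of the outcome is untouched.
- **That glucose fluctuation is affected in the same way**, because Table 2 lists "Flash glucose monitoring" at visits 1 and 5 only. The article gives no wear time or direction for the sensor, so nothing follows.
- **That the main result is at risk.** Body fat mass by bioelectrical impedance, and the sample size based on it, do not depend on the accelerometer.

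**What to change.** 1. Do the baseline wear in the existing 1-week run-in, before randomisation, and mark this in Table 2.
2. Do the follow-up wears in the seven days ending at visits 3 and 5, so that they match the questionnaire window.
3. Flag supervised-session time from the training log and report activity with and without sessions. This settles what basal means and keeps the end value interpretable once training falls inside the window.
4. State when randomisation and the first session occur relative to visit 1.

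The devices and the number of wears stay the same. The cost is a rescheduled hand-out: some devices go to people who are then not randomised, and controls, who attend only every four weeks, need the device at the preceding visit or by delivery. The primary analysis and the sample size do not change. The baseline change must be in place before a participant starts training, because a clean baseline week cannot be recovered afterwards.
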